### D90 (± 7 days)

- 4325 - Vital signs (O)
- 4326 - Urine pregnancy test
- 4327 - Hematology/ basic chemistry (O)
- 4328 - CRP, IgG, IgM (O)
- 4329 - Immunopathology
- 4330 - PCR of rAAV8 genome (O)
- 4331 - Visual Acuity, BCVA (ETDRS)
- 4332 - Basic ophthalmological exam
- 4333 - Contrast sensitivity (PR charts)
- 4334 - Flicker Fusion Frequency
- 4335 - Colour Constancy (chromatic adaption) (O)
- 4336 - Anomaloscopy
- 4337 - Cambridge Colour Test / Farnsworth D15
- 4338 - IR Video Pupillography
- 4339 - MP-1 Microperimetry (20°)
- 4340 - Funduscopy (mydriasis)
- 4341 - Dark adaptation test
- 4342 - ff-ERG (scotopic and photopic) (O)
- 4343 - sdOCT (O)
- 4344 - FAF (O)
- 4345 - FF
- 4346 - Angiography
- 4347 - Brief Symptom Inventory (BSI)
- 4348 - Psychological counselling
- 4349 - Study specific scale, A3-PRO
- 4350 - Adverse event recording
- 4351 - Concomitant medication
- 4352

[figure not shown]**Visit 9****D180 ( $\pm$  7 days)**

- Vital signs (O)
- Urine pregnancy test
- Hematology/ basic chemistry
- CRP, IgG, IgM (O)
- Immunopathology (O)
- PCR of rAAV8 genome (O)
- Visual Acuity, BCVA (ETDRS)
- Basic ophthalmological exam
- Contrast sensitivity (PR charts)
- Flicker Fusion Frequency
- Colour Constancy (chromatic adaption)
- Anomaloscopy
- Cambridge Colour Test / Farnsworth D15
- IR Video Pupillography
- MP-1 Microperimetry (20°)
- Funduscopy (mydriasis)
- Dark adaptation test
- ff-ERG (scotopic and photopic) (O)
- sdOCT (O)
- FAF (O)
- FF (O)
- Angiography (O)
- VFQ25
- Brief Symptom Inventory (BSI)
- Psychological counselling
- Study specific scale, A3-PRO
- Adverse event recording
- Concomitant medication

**Visit 10****D365, Close out ( $\pm$  14 days)**

- BMI
- Vital signs
- Urine pregnancy test
- Hematology/ basic chemistry
- CRP, IgG, IgM (O)
- Immunopathology (O)
- PCR of rAAV8 genome (O)
- Visual Acuity, BCVA (ETDRS)
- Basic ophthalmological exam
- Contrast sensitivity (PR charts)
- Flicker Fusion Frequency
- Colour Constancy (chromatic adaption)

[figure not shown]

- 4399 - Anomaloscopy
- 4400 - Cambridge Colour Test / Farnsworth D15
- 4401 - IR Video Pupillography
- 4402 - MP-1 Microperimetry (20°)
- 4403 - Funduscopy (mydriasis)
- 4404 - Dark adaptation test
- 4405 - ff-ERG (scotopic and photopic)
- 4406 - sdOCT
- 4407 - FAF
- 4408 - FF
- 4409 - Angiography
- 4410 - VFQ25
- 4411 - Brief Symptom Inventory (BSI)
- 4412 - Psychological counselling
- 4413 - Study specific scale, A3-PRO
- 4414 - Adverse event recording
- 4415 - Concomitant medication
- 4416

### 4417 **8.3. Follow-up Examinations**

4418

#### 4419 **Visit 11**

#### 4420 **Fup 1 M24 (± 1 month)**

- 4421 - Vital signs (O)
- 4422 - Hematology/ basic chemistry
- 4423 - CRP, IgG, IgM (O)
- 4424 - Immunopathology (O)
- 4425 - PCR of rAAV8 genome (O)
- 4426 - Visual Acuity, BCVA (ETDRS)
- 4427 - Basic ophthalmological exam
- 4428 - Contrast sensitivity (PR charts)
- 4429 - Anomaloscopy (O)
- 4430 - Cambridge Colour Test / Farnsworth D15 (O)
- 4431 - IR-Video-Pupillography (O)
- 4432 - MP-1 Microperimetry (O)
- 4433 - Funduscopy (mydriasis)
- 4434 - Dark adaption test (O)
- 4435 - ff-ERG (scotopic and photopic) (O)
- 4436 - sdOCT
- 4437 - FAF
- 4438 - FF
- 4439 - Angiography (O)
- 4440 - VFQ25 (O)
- 4441 - Study specific scale, A3-PRO
- 4442 - Adverse event recording
- 4443 - Concomitant medication
- 4444

[figure not shown]**Visit 12****Fup 2 M36 ( $\pm$  1 month)**

- Vital signs (O)
- Hematology/ basic chemistry
- CRP, IgG, IgM (O)
- Immunopathology (O)
- PCR of rAAV8 genome (O)
- Visual Acuity, BCVA (ETDRS)
- Basic ophthalmological exam
- Contrast sensitivity (PR charts)
- Anomaloscopy (O)
- Cambridge Colour Test / Farnsworth D15 (O)
- IR-Video-Pupillography (O)
- MP-1 Microperimetry (O)
- Funduscopy (mydriasis)
- Dark adaption test (O)
- ff-ERG (scotopic and photopic) (O)
- sdOCT
- FAF
- FF
- Angiography (O)
- VFQ25 (O)
- Study specific scale, A3-PRO
- Adverse event recording
- Concomitant medication

**Visit 13****Fup 3 M48 ( $\pm$  1 month)**

- Vital signs (O)
- Hematology/ basic chemistry
- CRP, IgG, IgM (O)
- Immunopathology (O)
- PCR of rAAV8 genome (O)
- Visual Acuity, BCVA (ETDRS)
- Basic ophthalmological exam
- Contrast sensitivity (PR charts)
- Anomaloscopy (O)
- Cambridge Colour Test / Farnsworth D15 (O)
- IR-Video-Pupillography (O)
- MP-1 Microperimetry (O)
- Funduscopy (mydriasis)
- Dark adaption test (O)
- ff-ERG (scotopic and photopic) (O)
- sdOCT
- FAF
- FF

[figure not shown]

- 4492 - Angiography (O)
- 4493 - VFQ25 (O)
- 4494 - Study specific scale, A3-PRO
- 4495 - Adverse event recording
- 4496 - Concomitant medication
- 4497
- 4498

## Visit 14

### Fup 4 M60 ( $\pm$ 1 month)

- 4501 - Vital signs (O)
- 4502 - Hematology/ basic chemistry
- 4503 - CRP, IgG, IgM (O)
- 4504 - Immunopathology (O)
- 4505 - PCR of rAAV8 genome (O)
- 4506 - Visual Acuity, BCVA (ETDRS)
- 4507 - Basic ophthalmological exam
- 4508 - Contrast sensitivity (PR charts)
- 4509 - Anomaloscopy (O)
- 4510 - Cambridge Colour Test / Farnsworth D15 (O)
- 4511 - IR-Video-Pupillography (O)
- 4512 - MP-1 Microperimetry (O)
- 4513 - Funduscopy (mydriasis)
- 4514 - Dark adaption test (O)
- 4515 - ff-ERG (scotopic and photopic) (O)
- 4516 - sdOCT
- 4517 - FAF
- 4518 - FF
- 4519 - Angiography (O)
- 4520 - VFQ25 (O)
- 4521 - Study specific scale, A3-PRO
- 4522 - Adverse event recording
- 4523 - Concomitant medication
- 4524

## 8.4. Non-ophthalmological and ophthalmological Procedures

All procedures should be performed in the sequence given by the flowchart, whenever possible. If feasible, the same investigators should perform the examinations for the study duration. Advanced test procedures, such as, but not limited to BCVA, microperimetry and pupillography, will be performed by study personnel after method-specific training.

If not specified differently, all tests described here will be performed according to the Flowchart of Visits and Procedures in *both* eyes.

All ophthalmological procedures will be performed in a fixed sequence, testing the study eye first and the fellow eye afterwards.

[figure not shown]

More details of all examination procedures can be found in the Procedure Manual in its current version as approved by the Principal Investigator.

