## **8. Examinations**

All study visits described in the flowchart, page 14, and in section 8.1. may be performed on two consecutive days; screening and close-out visit on three days if deemed necessary. The reason behind this is to reduce the workload due to concentration during test procedures and to improve the reliability of the test results.

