#### Ophthalmological procedures

All tests described will be performed in a fixed order. The treated eye will be examined first, followed by the untreated eye.

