#### 8.4.17. Infrared-Video-Pupillography

Pupillography is used for the objective efficacy assessment after intervention. Chromatic Pupillography will be performed at various time-points during the study as outlined in the flowchart of visits. Standardized adaptation, background illuminance, stimulus wavelength and duration need to be considered according to the Procedure Manual. Consensual measurement is performed, i.e. study eye is always stimulated while pupillary reactions of the fellow eye are recorded monocularly.

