#### 8.4.22. Spectral domain optical coherence tomography (SD-OCT)

Patients will be examined in mydriasis using a Spectralis HRT+OCT system (Heidelberg Engineering, Heidelberg, Germany). Briefly, perpendicular line and volume scans are recorded to quantify micro-anatomical changes in the macula before (baseline) and after (follow up) treatment. The patient is asked to look at a visual cue while eye-tracking software will correct for involuntary eye movement. Baseline recordings will be identified to allow precise follow-up recordings based on the same anatomical landmarks used for eye-tracking. The untreated eye will be recorded first, followed by the treated one.

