### ***10.4. Statistical Analysis***

AEs and SAEs will be documented using line listings and tabulations (MetraCad code will be applied). Descriptive analysis will include line charts for individual patients. Standard errors and means will be displayed also using line charts. This will be done for the raw measurements and for the difference between treated and untreated control eye within each patient.

Descriptive parameters will be given for the full cohort (n=9) but not for the sub-cohorts (n=3).

Additionally correlation analysis will be performed in a purely descriptive manner for the comparison of subjective and objective measurements. For each subject and measurement, the delta of the value for the interventional eye minus the mean of control eye values over time will be determined. In scatter plots for pairs of variables (measurements pooled over subjects) the association between these deltas will be displayed.

[figure not shown]

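### In the functional tests the study eye goes first in every patient, so test order cannot be separated from treatment in the planned treated-minus-fellow differences; subtracting screening would remove only the stable part

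*Supplement*

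**What the plan says.** All references are to protocol version 5.0.

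- **Order of testing.** Section 8.4 sets one sequence for all ophthalmological procedures, "testing the study eye first and the fellow eye afterwards". The heading Ophthalmological procedures repeats it: "The treated eye will be examined first, followed by the untreated eye". Neither place mentions alternation, a random order or a practice run.
- **Imaging.** SD-OCT (8.4.22) goes the other way: "The untreated eye will be recorded first, followed by the treated one". Autofluorescence (8.4.23) and fundus photography (8.4.24) have the same reversed order.
- **Pupillography.** In 8.4.17 the "study eye is always stimulated while pupillary reactions of the fellow eye are recorded monocularly". No recording with the fellow eye stimulated is described.
- **Fatigue.** Section 8 lets visits be split over two days (three for screening and close-out) "to reduce the workload due to concentration during test procedures" and to make the results more reliable.
- **Analysis.** Section 10.4 plots raw values and "the difference between treated and untreated control eye within each patient", as individual lines and as means with standard errors. For the correlation plots it uses "the delta of the value for the interventional eye minus the mean of control eye values over time". Neither quantity subtracts a baseline.
- **Setting.** The vector goes into the worse eye (Synopsis, Treatment). There is no masking or randomisation, and visual function is judged against the fellow eye (10.1). The efficacy measures are exploratory secondary endpoints (7.1).

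**The concern.** BCVA, contrast sensitivity, flicker fusion, the colour tests, microperimetry and dark adaptation all depend on the patient's effort and attention. The second eye may do better because the patient has just practised, or worse because the patient is tired. When the treated eye is first in every patient, any such effect has the same sign in all nine. It then forms part of what the plots show as the difference between treated and untreated eye. More patients would not shrink it, and no analysis can separate it afterwards, because no patient is tested in the other order.

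The fellow eye is the only comparator. Section 10.5 also plans an interim analysis to support negotiations with industrial sponsors about later development. It does not list the variables, but a displayed mean difference in visual function would be an obvious candidate.

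**Working it through.** **Inputs.** N = 3 × 3 = 9 (sections 3.1 and 10.2). The plan has no effect size, standard deviation or power to reproduce; 10.2 states that no sample size estimation was made. The size of an order effect is not given either. I assume d = 1, 3 or 5 letters between first- and second-tested eye.

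**Model.** At visit t:

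- treated eye: T(t) = μT + τ(t) + s(t) + a(t)
- fellow eye: F(t) = μF + s(t) + b(t)

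Here τ is the treatment effect (zero at screening), s is learning shared by both eyes, and a and b are the effects of being tested first or second. Write g(t) = a(t) − b(t).

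**Planned contrast.** T(t) − F(t) = (μT − μF) + τ(t) + g(t). It contains the baseline gap between the eyes and the whole order gap.

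**Change from screening in that contrast.** τ(t) + [g(t) − g(0)]. The baseline gap cancels, and so does a stable g. The functional tests are listed at screening (8.1) under the same order rule, so a same-order baseline exists.

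With no treatment effect (τ = 0), and leaving out μT − μF:

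| Assumed behaviour of the second eye | Raw difference, screening to D365 | Change from screening at D365 |
|---|---|---|
| Stable practice gain d | −d throughout | 0 |
| Stable fatigue d | +d throughout | 0 |
| Practice gain fades from d to 0 | −d to 0 | +d |
| Fatigue grows from 0 to d | 0 to +d | +d |
| Fatigue lessens from d to 0 | +d to 0 | −d |

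For d = 1, 3 and 5 the entries are 1, 3 and 5 letters with the signs shown.

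**Contrast for the correlation plots.** T(t) minus the mean of F over visits = (μT − μF) + τ(t) + [s(t) − mean s] + [a(t) − mean b]. Shared learning no longer cancels. If both eyes gain 1, 3 or 5 letters by D365, the delta rises by 1, 3 or 5 letters with no treatment effect.

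**Nine-patient mean.**

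- Fixed order: bias = 9d/9 = d.
- Alternation, five study-eye-first and four fellow-eye-first: bias = (5d − 4d)/9 = d/9 = 0.11, 0.33 and 0.56 letters for d = 1, 3 and 5.
- First eye drawn independently at random: expected bias 0, with a chance residual of SD d/√9 = 0.33d.

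**Against the standard error.** With an assumed SD of the eye difference of 3, 5 or 8 letters, SE = SD/√9 = 1.00, 1.67 or 2.67. At SD 5 and d = 3 the fixed-order bias is 3/1.67 = 1.8 SE. Across all the assumed values it runs from 1/2.67 = 0.4 SE to 5/1.00 = 5 SE.

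**Price of alternation in the raw plot.** Effects of +d in five patients and −d in four have sample variance (9d² − 9(d/9)²)/8 = 10d²/9. At d = 3 and SD 5 the displayed SD becomes √(25 + 10) = 5.9, and the SE 1.97 instead of 1.67. A stable effect drops out of each patient's change from screening, so this extra spread disappears there.

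**The case against.** The case against has several sound parts.

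- **Scope.** A reader might infer that every comparison between the eyes is affected. That does not hold. Three imaging procedures use the reverse order and depend little on practice. Pupillography describes no fellow-eye-stimulated value to compare. The ocular safety criterion of a 15-letter loss (7.2.1) is not defined as an eye difference.
- **Baseline.** A reader might also infer that subtracting baseline would not help. For a stable order effect it helps completely, and such an effect would show on the individual charts as an offset already present at screening. Only a changing effect survives, and nothing in the documents shows that one exists.
- **Direction.** It is tempting to say that the bias favours the treated eye. The table shows both signs. Nor can one assume that the study eye is tested untrained at screening. Section 5.2 says that suitable patients had already been invited to a non-invasive study, whose tests are not listed.
- **Mitigation.** Splitting visits over days may reduce fatigue, and the Procedure Manual, which is not shown, may provide rests or practice runs. Splitting a visit does not by itself change which eye goes first.
- **Consequence.** The affected endpoints are exploratory, and 10.4 specifies no hypothesis test.

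These points limit the concern but do not remove it. Section 10.4 as written plans the raw difference, not the change. In that quantity order and treatment coincide, and calling the analysis descriptive does not take the order effect out of the displayed mean.

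**Conclusion.** The point holds for the functional tests done in both eyes, in the raw treated-minus-fellow differences of 10.4. There, test order is fully confounded with treatment, and the same quantity also carries the baseline gap from treating the worse eye. Change from screening would clear the baseline gap and a stable order effect, but not an order effect that changes with practice or fatigue.

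An order gap of d letters enters the nine-patient mean in full, against d/9 under a 5:4 alternation. Both factors are exact under an additive order effect common to all patients. The letter values and the SDs are assumptions, so the ratios to the SE illustrate scale only. Neither the presence nor the sign of an order effect can be read from the documents. The weight is modest, because the endpoints are secondary and descriptive.

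**What to change.** 1. **Order.** In 8.4 and under Ophthalmological procedures, set the first-tested eye for the functional tests per patient, by alternation or a short random list balanced over the dose cohorts (for example 2:1, 1:2 and 2:1, which gives 5:4). Keep it at all visits and mark it on the individual charts. Patients already screened under the fixed order keep that order, so that their screening values remain a valid baseline. Version 5.0 is dated February 2017 and section 3.2 planned the last first visit for November 2016, so this step may reach few or no patients. Step 2 does not depend on it.
2. **Analysis.** In 10.4, report the change from screening in the treated-minus-fellow difference alongside the raw difference. State that a changing order effect remains for patients tested in the fixed order.
3. **Consistency.** Reconcile the wording in 8.4 and under Ophthalmological procedures, which covers all procedures, with the reverse order in 8.4.22 to 8.4.24, for instance by naming the imaging tests as exceptions.

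**Cost.** No extra tests, visits or staff are needed. Steps 1 and 3 change the protocol and, where it repeats the order, the Procedure Manual. Section 13 requires approval of an amendment by the regulator and the ethics committee, and a revised patient information form signed by all patients. Alternation also puts order effects of opposite sign on the individual charts and adds some between-patient spread to the raw differences.

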#### **8.4.1. Medical / surgical history**

Essential events have to be documented in the patient file / worksheet with dates of onset and underlying pathology.

#### **8.4.2. Ocular / surgical history**

Any ophthalmological disease or surgery in either eye has to be documented with date of onset.

#### **8.4.3. Body Mass Index**

Deriving from height and weight of the patient, the BMI (kg/m^2) will be calculated.

#### **8.4.4. VIIs**

After 10 minutes resting in a sitting position blood pressure, heart rate and body temperature will be measured.

#### **8.4.5. Urine pregnancy test**

In female subjects with childbearing potential a commercial urine pregnancy test will be performed by the study nurse / study coordinator at all marked visits.

#### **8.4.6. Hematology, basic chemistry and urine analysis**

The following parameters will be tested at those visits where blood and urine tests are foreseen:

- Sedimentation rate
- Differential Blood count
- Hemoglobin
- Hematocrit
- Platelet count
- Glucose
- Sodium
- Potassium
- Uric acid
- Creatinine
- Creatinine kinase
- LDH
- Total bilirubin
- Direct bilirubin
- AST (SGOT)

[figure not shown]

- ALT (SGPT)
- $\gamma$ GT
- Alkaline phosphatase
- Proteine electrophoresis
- Coagulation (INR, PTT, aPTT)
- Urine analysis

#### 8.4.7. CRP, Immunoglobulines

CRP, IgG and IgM will be determined at all marked study visits.

#### 8.4.8. Immunopathology

In a specialized local lab ([name]) anti-AAV8 capsid ELISA will be determined.

#### 8.4.9. PCR of rAAV8 genome

A search for potential systemic rAAV8 virus genome will be performed at early study visits and later on if a control is deemed necessary by the investigator.

#### Ophthalmological procedures

All tests described will be performed in a fixed order. The treated eye will be examined first, followed by the untreated eye.

#### 8.4.10. Best corrected visual acuity

Best corrected visual acuity will be quantified using the ETDRS visual acuity protocol as described in the Procedure Manual.

#### 8.4.11. Basic ophthalmological examination

After determination of visual acuity, outer eye segments will be inspected and the anterior segments of the eye will be examined using a slit-lamp.

#### 8.4.12. Contrast sensitivity (Pelli Robson Charts)

This test for contrast sensitivity will be performed in both eyes at standardized illumination conditions, according to the Procedure Manual of the Pelli Robson (PR) chart. In contrast to the user instruction of the PR chart, the test distance will be 3m (instead of 1m), as own data have shown, that the standard distance of 1m is inferior in sensitivity.

#### 8.4.13. Flicker Fusion Frequency

The Flicker Fusion Frequency is used to test cone function independent of selective amblyopia problems eventually present. The subject increases flicker frequency until disappearance of flicker sensation.

#### 8.4.14. Colour constancy

Patients are asked to judge the chromatic appearance of a hexagonal test patch within a multi-coloured display at photopic levels. More details are described in the Procedure Manual.

#### 8.4.15. Anomaloscopy

The Nagel anomaloscope can differentiate between six pathological findings i.e. colour deficiencies and will be used in the trial to investigate baseline and possible restitution of colour discrimination. The Rayleigh-equation quantitatively evaluates results.

#### 8.4.16. Cambridge Colour Test / Farnsworth D15

Chromatic discrimination thresholds will be determined using the low-vision version of the Cambridge Colour Test as described in more detail in the Procedure Manual. The stimulus array consists of discrete dots of variable random size and luminance. The target is a subset of dots, which delineate a large 5-degree square varying in saturation. Patients indicate the location of the coloured square in an alternative forced choice procedure.

The D15 set is a modification of the well-known Farnsworth-Munsell 100 Hue Test. The D15 test is intended for classification instead of more time-consuming in-depth study of color vision defects using the 100-Hue test. Each D15 set contains a reference disc and fifteen numbered discs, which make up an incomplete color circle. Following an attempt to sequentially arrange the discs by the patient, evaluation determines color perception or defects in deutan, protan or tritan axis discrimination. Sometimes there are indeterminate defects in the cases of retinal toxicity.

#### 8.4.17. Infrared-Video-Pupillography

Pupillography is used for the objective efficacy assessment after intervention. Chromatic Pupillography will be performed at various time-points during the study as outlined in the flowchart of visits. Standardized adaptation, background illuminance, stimulus wavelength and duration need to be considered according to the Procedure Manual. Consensual measurement is performed, i.e. study eye is always stimulated while pupillary reactions of the fellow eye are recorded monocularly.

#### 8.4.18. Microperimetry

Microperimetry tests retinal sensitivity by projecting defined light stimuli to specific locations within the macula under mesopic conditions. The subjects are asked to press a button when a stimulus is perceived. Involuntary eye movements are corrected in real-time and fixation stability is quantified. This test will be performed according to the Procedure Manual.

**Note: All following tests will be performed in pharmacologically induced mydriasis (2.5% phenylephrin, 0.5% tropicamid eye drops) only.**

